**G) Study design**

materials and methods

Subject Selection

All subjects volunteering for participation in the study will be screened using the following inclusion and exclusion criteria. Approximately 30 subjects with moderate to severe plaque psoriasis will be entered into the study.

Inclusion Criteria

Subjects must meet the following inclusion criteria to be eligible for study entry:

- Signed informed consent
- Plaque psoriasis covering >10% of total BSA
- Diagnosis of plaque psoriasis for at least 6 months
- PASI score >=12 (see Appendix A) or Linear PASI score of >= 8.0 at screening (see Appendix B).
- In the opinion of the investigator, candidate for systemic therapy for psoriasis:

A. Who has not been previously treated (naive to systemic treatment) OR

B. Who has had prior treatment with systemic therapy for psoriasis (e.g., PUVA, cyclosporine, corticosteroids, methotrexate, oral retinoids, mycophenolate mofetil (MMF), thioguanine, hydroxyurea, sirolimus, azathioprine, 6‑MP, etanercept)

- Body weight of <140 kg
- 18 to 75 years old. As the risk of Efalizumab in childhood is unknown, those < 18years will be excluded from the study.
- For women of childbearing potential or in men whose partners may become pregnant, willingness to use an acceptable method of contraception to prevent pregnancy for the duration of the study (while receiving study medication and 3 months following). Acceptable methods of contraception include use of a condom; abstinence; use by sexual partner of oral implantable or injectable contraceptives, IUD, female condom, diaphragm with spermicide, cervical cap; or a sterile sexual partner
- Willingness to hold sun exposure reasonably constant and to avoid use of tanning booths or other UV light sources during the study

Exclusion Criteria

Subjects who meet any of the following exclusion criteria are ineligible for study entry:

- Guttate, erythrodermic, or pustular psoriasis as sole or predominant form of psoriasis
- History of severe allergic or anaphylactic reactions to humanized monoclonal antibodies or fusion proteins that contain an Ig Fc region
- Clinically significant psoriasis flare during screening or on the first treatment day
- Treatment with efalizumab (anti-CD11a) within the last 12 months before enrollment
- Pregnancy or lactation. As the risk of Efalizumab in pregnancy is unknown, pregnant women will be excluded from the study.
- History of or ongoing uncontrolled bacterial, viral, fungal, or atypical mycobacterial infection
- History of active tuberculosis (TB) or currently undergoing treatment for TB. PPD testing or chest X-ray is required for high‑risk subjects (see Appendix D). Subjects with a positive PPD (not due to BCG vaccination) or chest X-ray will be excluded
- History of opportunistic infections (e.g., systemic fungal infections, parasites)
- Seropositivity for human immunodeficiency virus (HIV)
- Seropositivity for hepatitis B or C virus
- Hepatic enzymes >3 times the upper limits of normal (ULN)
- Diagnosis of hepatic cirrhosis, regardless of cause or severity
- WBC count <4000L or >14,000/L
- Serum creatinine >2 times the ULN
- Hospital admission for cardiac disease, stroke, or pulmonary disease within the last year
- Presence of malignancy within the past 5 years, including lymphoproliferative disorders. Subjects with a history of fully resolved basal cell or squamous cell skin cancer may be enrolled.
- History of substance abuse within the last 5 years
- Any medical condition that, in the judgment of the investigator, would jeopardize the subject’s safety following exposure to study drug

Note: Certain medications and vaccines may not be used for specified periods of time prior to enrollment or at any time during the treatment period. Please see text on page 21 and 22 regarding excluded therapies.

Study Treatment

Formulation

Efalizumab (Raptiva) is manufactured by Genentech. Efalizumab is supplied in single‑use glass vials containing 125 mg of sterile, pyrogen‑free, lyophilized drug product. When reconstituted with 1.3 mL of Sterile Water for Injection (SWFI), each vial contains efalizumab at a concentration of 100 mg/mL. The solution is clear. Reconstituted efalizumab is composed of efalizumab (125 mg), polysorbate 20, L‑histidine hydrochloride, sucrose, and SWFI, USP at a pH of 6.2.

For further details, see the Investigator Brochure.

Dosage, Administration, and Storage

Each subject will receive 24 weekly doses of 1.0 mg/kg study drug. Study drug will be administered by SC injection.

The following formula will be used to calculate dose volume:

| Dose volume (mL) = | Assigned dose (mg/kg)  body weight (kg) |
| --- | --- |
| 100 (mg/mL) |

4.3.3 Dosage Modification

a. Change in Injection Volume

At any clinic visit during which study drug is administered, if a subject’s body weight has changed by 10% from the body weight used for the calculation of the previous injection volume, a new injection volume should be calculated based on the new body weight.

b. Missed Doses

Missed doses will not be replaced.

If a subject misses a dose of study drug (e.g., Treatment Day 7), dosing should resume with the next scheduled dose (e.g., Treatment Day 14).

Assessments during Treatment (Study Flowchart Appendix H)

All procedures should be completed prior to dosing.

Visit tolerance dates are +/-2 days from the schedule relative to Day 0.

- - - - 1. Day 0 (First Treatment Day)
- Review of inclusion and exclusion criteria
- Review and update of medical history for any interim events between screening and Day 0
- Complete physical examination, including dermatologic examination
- Vital signs (pre-dose; blood pressure while the subject is seated, pulse rate, and body temperature)
- Body weight and calculation of conditioning dose- faxed to pharmacy
- PASI score (Appendix A)
- Linear PASI Score (Appendix B)
- Psoriatic BSA (Appendix C)
- Medical photographs
- Review and recording of concomitant medications
- Skin biopsy (6mm punch biopsies of normal and psoriatic skin)
- Skin biopsy (optional small shave biopsies, approximately 1 cm by 1 cm, of normal and psoriatic skin)
- Research blood tests (see table Appendix F)
- Hematology: CBC with differential and platelet count
- Urine pregnancy test (predose; for women of childbearing potential only). If test results are positive, confirm findings with a serum pregnancy test. Do not administer study drug unless the serum pregnancy test result is negative.
- Administration of study drug (see Appendix E)
- Monitoring and recording of any adverse events following administration of study drug
- Subject Instruction Sheet

**b. Day 7 (Week 1)**

- Vital signs
- Body weight and dose calculation
- Review and recording of concomitant medications
- Monitoring and recording of adverse events
- Administration of study drug

**c.** **Day 14 (Week 2)**

- Vital signs
- Body weight and dose calculation
- PASI score and Linear PASI score, Psoriatic BSA
- Review and recording of concomitant medications
- Medical photographs
- Research blood
- Hematology: CBC with differential and platelet count
- Skin biopsy (6mm punch biopsies of psoriatic skin)
- Skin biopsy (optional small shave biopsies, approximately 1 cm by 1 cm, of normal and psoriatic skin)
- Monitoring and recording of adverse events
- Administration of study drug

d. Day 21 (Week 3)

- Vital signs
- Body weight and dose calculation
- Review and recording of concomitant medications
- Monitoring and recording of adverse events
- Administration of study drug

e. Day 28 (Week 4)

- Vital signs
- Body weight and dose calculation
- Review and recording of concomitant medications
- Urine pregnancy test
- Monitoring and recording of adverse events
- Administration of study drug
- Research blood

f. Day 35 (Week 5)

- Vital signs
- Body weight and dose calculation
- Review and recording of concomitant medications
- Monitoring and recording of adverse events
- Administration of study drug

g. Day 42 (Week 6)

- Vital signs
- Body weight and dose calculation
- Review and recording of concomitant medications
- PASI score and Linear PASI score, Psoriatic BSA
- Medical photographs
- Skin biopsy (6mm punch biopsy of psoriatic skin)
- Research Blood
- Hematology: CBC with differential and platelet count
- Monitoring and recording of adverse events
- Administration of study drug

h. Day 49 (Week 7)

- Vital signs
- Body weight and dose calculation
- Review and recording of concomitant medications
- Monitoring and recording of adverse events
- Administration of study drug

i. Day 56 (Week 8)

- Vital signs
- Body weight and dose calculation
- Review and recording of concomitant medications \
- Urine pregnancy test
- Monitoring and recording of adverse events
- Administration of study drug
- Research blood

j. Days 63, 70, and 77 (Week 9, 10, 11)

- Vital signs
- Body weight and dose calculation
- Review and recording of concomitant medications
- Monitoring and recording of adverse events
- Administration of study drug

k. Day 84 (Week 12)

- Complete physical examination, including dermatologic evaluation
- Vital signs
- PASI score and Linear PASI score, Psoriatic BSA
- Medical photographs
- Review and recording of concomitant medications
- Skin biopsy (6mm punch biopsy of psoriatic skin; an additional skin biopsy will be taken if the target lesion is not representative)
- Skin biopsy (optional small shave biopsies of psoriatic skin, approximately 1 cm by 1 cm, optional)
- Research blood
- Hematology: CBC with differential and platelet count
- Urine pregnancy test
- Monitoring and recording of adverse events
- Instruction of medication administration

**l. Days 112, 140, and 168 (Weeks 16, 20, 24)**

- Vital signs
- PASI score and Linear PASI Score, Psoriatic BSA
- Research blood-optional
- Hematology: CBC with differential and platelet count-if research blood drawn
- Biopsy of psoriatic skin (6mm punch biopsy) and medical photographs will be done when and if relapse should occur. Relapse is defined as loss of >=50% of PASI improvement compared to baseline. An additional biopsy and medical photographs could also be taken, if and when morphologically unusual lesions develop, even if the definition of relapse (>=50 loss of original PASI improvement) is not met.
- Review and recording of concomitant medications
- Monitoring and recording of adverse events
- Urine pregnancy test monthly
- Complete physical examination, including dermatologic evaluation at Day 168

Concomitant and excluded Therapies

Concomitant Therapy

- The concomitant psoriasis medications that may be used during the study (screening and treatment periods) are:
- Emollients (e.g., petrolatum or Eucerin cream or lotion)
- Tar or salicylic acid for scalp psoriasis
- Potency Group VI or VII topical corticosteroids in small amounts for psoriatic lesions on the face, hands, feet, groin, or axillae

Emollients, scalp preparations, and topical corticosteroids should not be used on psoriatic lesions on the day of a scheduled clinic visit when a PASI evaluation will be performed. If desired, these agents may be applied after the clinic visit has been completed.

Acetaminophen will be administered prior to the administration of the first three doses to reduce the incidence and severity of flu-like symptoms (i.e., headache, chills, fever, nausea, vomiting, and myalgia) sometimes seen following efalizumab administration. If acetaminophen is ineffective or if the subject is allergic to acetaminophen, ibuprofen can be administered at the discretion of the investigator. Alternatively, subjects may be pretreated with non-steroidal, non-prescription analgesics at the Investigator’s discretion. If a subject experiences an acute adverse event of nausea or vomiting, the subject may be treated with any approved anti‑emetic, as required.

If a subject experiences acute adverse events (defined as fever, headache, chills, nausea, vomiting, or myalgia on the day of or the 2 days following an injection of study drug), acetaminophen or other nonprescription, nonsteroidal analgesics are recommended as the first therapy. If these are ineffective, any approved analgesic may be prescribed at the discretion of the investigator. If a subject experiences nausea or vomiting, the subject may be treated with any approved anti‑emetic, as required.

If a subject experiences relapse of psoriasis after withdrawal from efalizumab, systemic or UV therapy may be used to the investigator’s discretion.

Treatment regimens of ‑blockers, angiotensin-converting enzyme (ACE) inhibitors, antimalarial drugs, quinidine, interferon, or lithium should be held constant, if possible, between Day –28 and Day 84. Addition or changes in these medications do not require discontinuation from the study.

Excluded Therapies

The following concomitant therapies are excluded for specified times prior to enrollment and throughout the treatment period:

- Systemic treatments for psoriasis (e.g., PUVA, cyclosporine, corticosteroids, methotrexate, oral retinoids, MMF, thioguanine, hydroxyurea, sirolimus, azathioprine, 6-MP, etanercept) (excluded from Day –28 of the screening period through Day 84)
- Immunosuppressive medications for any indication (excluded from Day –28 through Day 84)
- Live virus or bacteria vaccines, which include, but are not limited to, measles, mumps, rubella, polio, bacille Calmette‑Guerin (BCG), yellow fever, and TY21a typhoid (excluded from Day –14 through Day 84)
- Concomitant experimental drugs or treatments (excluded from Day –28 or five half-lives, whichever is longer, prior to Day 0 through Day 84)

If a subject receives one of the above medications during the screening period, the subject should not be included. If a subject receives one of these excluded concomitant therapies during the treatment period, the subject should not receive any additional doses of study drug and should be discontinued from the study.

The following additional concomitant therapies should be discontinued for at least 14 days prior to treatment:

- UVB phototherapy, tanning booths, or other nonprescription UV light sources
- Topical treatments for psoriasis (e.g., Potency Group I and II topical corticosteroids, calcipotriene, tazarotene, anthralin).
- Vaccines that do not contain live viruses or bacteria (e.g., flu, Pneumovax , tetanus)

These vaccines may not be effective when administered in the presence of therapeutic circulating levels of Efalizumab.

Instructions to Subjects

The following instructions should be given to subjects:

- All medications being used must be reported to the investigator.
- Donations of blood or blood products are not allowed during the study and for at least 3 months following the last injection of study drug.
- Treatment with immunotherapies such as killed virus vaccines, toxins, and allergy desensitization may not be effective during therapy with Efalizumab.

Subjects who require such vaccines (e.g., tetanus toxin booster, influenza vaccine) should be encouraged to schedule these at least 14 days prior to Day 0 or at least 3 months following the last injection of study drug.

- Vaccines that contain live organisms (e.g., BCG, measles) should not be administered in the presence of study drug (Day–14 through Day 84).
- If any new drugs are prescribed by any health care provider during a subject’s participation in the study, the subject should notify the prescribing physician of his or her participation in this study and notify the study staff of the new medications.
- Tanning beds, booths, or home UV light sources are prohibited from
  Day –14 through Day 84.
- If the subject experiences acute adverse events, such as headache, fever, chills, myalgia, nausea, or vomiting 12–48 hours following SC injection of study drug, the subject may be provided with the recommended therapy. Headache, fever, chills, or myalgia may be treated with acetaminophen or other nonprescription analgesic, if needed. Nausea or vomiting may be treated with an approved anti-emetic as needed. If the symptoms are severe, the subject should contact the investigator.
- Allergic reactions or hypersensitivity reactions such as hives or throat tightness should be reported immediately to the investigator. The subject should also seek immediate medical attention.
- Signs and symptoms of an infection should be promptly reported to the investigator.

See appendix G for a detailed patient information sheet taken from the drug label.

These instructions apply through Day 84. Subjects will receive a written instruction sheet on Day 0.

Compliance with Laws and Regulations

This study will be conducted according to the International Conference on Harmonization E6 Guideline for Good Clinical Practice (GCP) and any federal, national, and local requirements.

Subject Discontinuation

Subjects may withdraw or be withdrawn from the study, at any time. Every effort will be made to obtain information on subjects who discontinue from the study prematurely. The procedures and assessments to be performed at the end of treatment visit will be the same as those for the Day 84 visit.

Criteria for Discontinuation of Treatment

The criteria for discontinuation of treatment include the following:

- Pregnancy
- Administration of a live virus or bacteria vaccine
- Initiation of excluded systemic treatment for psoriasis
- Initiation of excluded immunosuppressive treatment for any indication
- Initiation of excluded experimental medication or other treatment
- Any medical condition (e.g., opportunistic infections, malignancies, immune complex disorders) that the investigator determines may jeopardize the subject’s safety if he or she continues in the study.

Study Discontinuation

Genentech has the right to terminate this study at any time. Reasons for terminating the study may include the following:

- The incidence or severity of adverse events in this or other studies indicates a potential health hazard to subjects.

1. **Statistical Model**

Preliminary data suggest that patients responding to efalizumab have lower expression levels of cytokines associated with activation of T-cells (IL-12, -IFN, IL-8, iNOS, and STAT1) than patients not responding. The response had been determined by the expression of K16 mRNA and epidermal thickness on day 56.

To correlate overall response with overall cytokine expression, response and cytokine expression were scored using a novel application of u-statistics to multivariate data. In short, the (response or cytokine expression) profile of each patient (A) is compared one-by-one with the profiles of all other patients (Xi). If patient A has a higher observation for each of the (response or cytokine expression) variables than patient Xi, the score of patient A is increased by one, if all Xi variables are lower, the score is decreased by one. If some variables have higher observations, while others have lower observations, the score of patient remains unchanged.

The response score correlated well with histological findings. Patients judged independently as complete responders were assigned scores between 2.5 and 5.5, partial responders were assigned scores between –2.0 and 0.5; non-responders between –5.5 and –3.5. Epidermal CD3+ T-cells on day 56 had a week correlation of .52 with the response score, while dermal CD3+ T-cells were virtually uncorrelated (r=0.12). The T-cell pathway score for both types of CD3+ T-cells was 0.38.

The correlation of u scores for individual cytokines on day 56 with the response score ranged from 0.18 (-IFN) to 0.66 (IL-12). The inflammation pathway score based on the expression of all five cytokines was 0.80. The correlation was smaller for all subsets, indicating that all cytokines contribute, as one would expect from cytokines on a single pathway. Eliminating a single variable from the pathway score had the smaller effects on the correlation for IL12 (-0.01) and -IFN (-0.03) than for IL-8 (-0.07), STAT1 (-0.19), and iNOS (-0.21), consistent with the hypothesis that the latter cytokines are further “downstream”.

Among the 12 patients in this study, three patients were neither superior nor inferior to any other patient and, thus, could not be assigned an informative score. Comparing the remaining four patients with a positive response score to the five patients with a negative response score by the pathway score yielded test statistic of 6.102 (2, 1 d.f.). While this is nominally significant (p = 0.0135, exact), it cannot be excluded that results based on a study where the smaller group has only four patients are confounded.

Since this is a mechanism of action study, where the consequences of false negative results (not continuing research on an important mechanism of action) are at least as severe as the consequences of false positive results (doing more research on the current drug, even if the mechanism of action should turn out to be different). Therefore, level () and power (1-) need to be chosen so that  for. Thus, to achieve the conventional 5% level, a power of at least 95% would be required. Assuming t the within group variation and correlation of the data observed above is representative for data in the proposed study, the above test statistic of 6.102 can be interpreted as the non-centrality parameter of the chi-square distribution with 1 df.

The non-centrality parameter required to guarantee 95% power at the 5% level (two-sided) is 14.37. In the previous study of twelve patients, three patients (25%) were uninformative, because their results were uniquely ambiguous. Thus, a total sample size of 14.37/6.102*9*1.25=27 per group would be required to detect an effect as large as seen in the previous study with 95% power at the 5% level (two-sided). It is common for up to 10% of the enrolled patients to not complete the entire treatment protocol. Thus, we plan to enroll approximately 30 patients to allow for this possibility.

While we have chosen the expression of cytokines at day 84 as the primary outcome, we will also explore whether changes in cytokine expression at different points in time may even be more closely correlated with response.

As the mechanism of action is presently unknown, it cannot be determined, whether (a) differences in expression, (b) ratios in expression, or (c) ratios in expression above the expression in non-lesional skin are the most relevant parameters to measure changes in cytokine activity. Therefore, we will use a non-parametric approach, again based on u-statistics. In brief, we will consider a change in patient A larger than in patient B, if patient A has higher expression than patient B at the first and a lower expression than patient B at the second time point. If for neither patient the pre-post expression interval is included in the other patient, this pair of patients will not affect the computation of these patients’ u-scores. Replacing the set of cytokine levels with a set of cytokine changes and selecting for each cytokine a different time interval will allow us to explore the hypothesis that cytokines further downstream contribute earlier to the activity along the pathway.

11. Study Subjects:

Adults with plaque psoriasis covering > 10% of body surface area (BSA) and a PASI score of > 12.0 or linear PASI score >=8 at screening who are candidates for systemic psoriasis therapy, will be entered into the study. A subject is considered a candidate for systemic therapy if assessed by a clinician as requiring systemic therapy (e.g., psoralen with UV light [PUVA], cyclosporine, corticosteroids, methotrexate, oral retinoids, mycophenolate mofetil [MMF], thioguanine, hydroxyurea, sirolimus, azathioprine, 6-MP, etanercept) to control psoriasis, whether or not that subject has a history of receiving systemic therapy. Approximately 30 subjects will be enrolled.

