**10. Abstract, Rationale of Study, Research Plan and Procedures:**

- **Abstract**

This is a 24-week study with Efalizumab, a biologic agent injected subcutaneously once weekly. The dose administered is 1 mg/kg of body weight. Patients are seen weekly for the first 12 weeks and they are injected with the medication in our outpatient clinic. Patients are instructed to mixing and self-administering the medication to themselves, and administer the medication to themselves for the second 12 weeks of the study. They are then seen every other week in the outpatient clinic. Skin biopsies are performed before, during, and after the study. Clinical assessments and photography will parallel the skin biopsies. Patients will be evaluated at each visit for any adverse events and safety labs will be taken monthly.

- **Rationale of Study, Research Plan and Procedures**

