As of 16 June 2003, 23 serious adverse events that occurred in Studies ACD2058g, ACD2059g, ACD2600g, ACD2601g, ACD2062g, ACD2243g, and ACD2390g and have been filed as Investigational New Drug (IND) safety reports: laryngospasm, thrombocytopenia (8 cases-see below), Legionella pneumonia, exfoliative erythroderma, elevated liver function test results, vertebral osteomyelitis, fever, squamous cell carcinoma, Hodgkin’s lymphoma, pneumonia, abscess of the left leg, surgical wound abscess, inflammatory arthritis, priapism, pustular psoriasis of Von Zumbusch, demyelinating process, adenopathy, allergic drug reaction, sinusitis, equilibrium disturbance, and eosinophilic pneumonitis.

In the combined safety database of 2762 patients, there were eight occurrences (0.3%) of thrombocytopenia of <52,000 cells per ul reported. Three of the eight patients were hospitalized for thrombocytopenia, including one patient with heavy uterine bleeding; all cases were consistent with an immune mediated thrombocytopenia. Antiplatelet antibody was evaluated in one patient and was found to be positive. Each case resulted in discontinuation of efalizumab. Based on available platelet count measurements, the onset of platelet decline was between 8 and 12 weeks after the first dose of efalizumab in 5 of the patients. Onset was more delayed in 3 patients, occurring as late as one year in 1 patient. In these cases, the platelet count nadirs occurred between 12 and 72 weeks after the first does of efalizumab. (This information is taken from the drug label.)

Four deaths have occurred that were determined by the investigators to be unrelated to study drug.

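### The platelet count at Days 112, 140 and 168 depends on an optional research draw, which conflicts with the monthly safety laboratory tests stated in the abstract

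*Protocol*

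**What the plan says.** The abstract (section 10) states: "Patients will be evaluated at each visit for any adverse events and safety labs will be taken monthly". Section 15, Procedures to Minimize risks, lists hematology first among the routine safety laboratory tests, with chemistry and urinalysis.

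The visit list under Assessments during Treatment has the line "Hematology: CBC with differential and platelet count" without any condition at Days 0, 14, 42 and 84. At Days 112, 140 and 168 it has "Research blood-optional", followed by "Hematology: CBC with differential and platelet count-if research blood drawn". The monthly urine pregnancy test in that same list carries no such condition. Days 28 and 56 list research blood but no blood count.

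Subject Discontinuation adds: "The procedures and assessments to be performed at the end of treatment visit will be the same as those for the Day 84 visit". The Day 84 procedures include the blood count.

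Dosing is 24 weekly injections, given in the clinic for the first 12 weeks and self-injected in weeks 13 to 24.

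**The concern.** A test that the protocol classes as a safety assessment has been tied to a research sample that the patient may refuse. Staff working from the visit list would omit the count in a patient who declines. Staff working from the abstract would take it.

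The test matters because of the protocol's own account under Clinical Experience with Efalizumab. Eight cases of thrombocytopenia below 52,000 cells per µL are reported in 2762 patients. All were consistent with an immune mechanism, three patients were hospitalized, and every case led to stopping the drug. On timing, the protocol says "the onset of platelet decline was between 8 and 12 weeks after the first dose of efalizumab in 5 of the patients" and "Onset was more delayed in 3 patients, occurring as late as one year in 1 patient". Nadirs are put at weeks 12 to 72, although the wording leaves open whether that range covers all eight cases or only the three late ones.

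The count therefore becomes optional in a period when a decline that began in weeks 8 to 12 may still be deepening and when later cases can start. It is also the period when injections move from the clinic to the patient. The decision to stop treatment for a medical condition rests with the investigator, who needs a count to see a platelet decline before symptoms appear.

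**Working it through.** The check sets the listed counts against the dosing calendar.

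**Inputs**
- Doses: 24, weekly from Day 0 (Dosage, Administration, and Storage). The last dose is at Day 7 × 23 = 161.
- Order: procedures come before dosing at each visit (Assessments during Treatment).
- Unconditional counts: Days 0, 14, 42 and 84 (visit list).
- Conditional counts: Days 112, 140 and 168 (visit list).
- Stated frequency: monthly (abstract), taken here as every 28 days.
- Thrombocytopenia: 8 of 2762 (Clinical Experience with Efalizumab).
- Sample size: about 30.

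**After Day 84, patient declines research blood**
- Doses at Days 84, 91, 98, 105, 112, 119, 126, 133, 140, 147, 154 and 161: 12 doses after the Day 84 count.
- Unconditional counts listed after Day 84: 0. If the end-of-treatment rule also covers patients who complete treatment, there is 1, at Day 168. A monthly schedule gives 3.
- A Day 168 count would come 168 − 161 = 7 days after the last dose and could not guide any of the 12. The gap from Day 84 to Day 168 is 84 days.

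**Up to Day 84**
- Gaps between unconditional counts: 14, 28 and 42 days.
- Post-baseline counts: 3 (Days 14, 42 and 84) in 12 weeks, the same number that a monthly schedule gives.
- Doses from the Day 42 count to the Day 84 count: Days 42, 49, 56, 63, 70 and 77, so 6.

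**Effect of the changes**

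| Unconditional count days | Longest gap to Day 84 | Longest gap after Day 84 | Most doses between counts, to / after Day 84 |
|---|---|---|---|
| As listed: 0, 14, 42, 84 | 42 days | 84 days (to Day 168) | 6 / 12 |
| Condition removed: add 112, 140, 168 | 42 days | 28 days | 6 / 4 |
| Also add 56 | 28 days | 28 days | 4 / 4 |
| Also add 28 | 28 days | 28 days | 4 / 4 |

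The last row shows that a Day 28 count does not improve either measure.

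**Expected cases in 30 patients, from the crude proportion**
- Any time: 30 × 8/2762 = 0.087.
- Beginning in weeks 12 to 24: three of the eight cases started later than weeks 8 to 12, one of them at about a year. So 0 to 2 of the eight could fall here, giving 0 to 30 × 2/2762 = 0.022.

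**The case against.** The strongest reply is that the full laboratory schedule is not in view. The visit list refers to the Appendix H flowchart, which is not in the text at hand. The list is visibly not the whole schedule: chemistry and urinalysis appear at no listed treatment visit, and the abstract says of weeks 13 to 24 "They are then seen every other week in the outpatient clinic", whereas the list gives only four-weekly visits. A separate monthly safety panel may be shown in Appendix H, and the conditional count may be one tied to research sampling.

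This limits the claim but does not remove it. After Day 84 the count is not merely left out of the list; it is entered with an explicit condition. If Appendix H does require monthly counts, that line contradicts the flowchart as well as the abstract and still needs correcting. A reader might infer that the protocol as a whole requires no platelet count after Day 84. The documents do not support that.

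A second reply concerns the first 12 weeks. A reader might infer that the missing counts at Days 28 and 56 also breach the monthly promise. That does not hold up. Three post-baseline counts by Day 84 match a monthly number, the abstract sets no maximum interval, and Day 84 itself has an unconditional count at the end of the week 8 to 12 onset window. What remains is one 42-day gap, which is a reason to consider a Day 56 count and no more.

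Third, the harm needs several things together: a patient who declines blood at both Day 112 and Day 140, staff who follow the list over the abstract, and a rare event. Patients who stop early are covered, because the end-of-treatment rule stands under Subject Discontinuation and brings the Day 84 procedures with it. All of this is fair and keeps the point modest.

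**Conclusion.** The conflict is real and should be fixed. On the visit list as written, a patient who refuses research blood and continues treatment can self-inject 12 doses with no unconditional platelet count between Day 84 and Day 161. The abstract and section 15 together imply monthly hematology.

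This rests on reading monthly as roughly every 28 days and on the visit list as it stands, with Appendix H unseen. Whether a completer has a required count at Day 168 depends on whether the end-of-treatment rule extends beyond early stoppers, which the text does not settle.

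This is a patient-safety point of small expected size: about 0.09 cases in 30 patients overall, and between 0 and about 0.022 beginning in weeks 12 to 24. Those figures carry a crude proportion from the wider safety database over to this trial without adjusting for length of exposure. Nothing here bears on the primary inference at Day 84. The case for acting is that the text contradicts itself on a named safety test and that the repair is cheap.

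**What to change.** In the list for Days 112, 140 and 168, delete the condition attached to the hematology line, so that the blood count with differential and platelets is an unconditional safety test at all three visits. Make Appendix H agree.

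Optionally, add the same count to the research draw that already exists at Day 56. This closes the 42-day gap and places a count at the start of the week 8 to 12 onset window. A Day 28 count is not needed.

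Cost: at most 3 routine counts per patient, 3 × 30 = 90 in total, or 4 × 30 = 120 with Day 56. All fall at visits already listed. A small extra draw is needed only at Days 112, 140 and 168, and only in patients who decline research blood.
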